### Ethics and dissemination

This study, protocol and all measures, including the informed consent document, have been approved by Human Research Ethics Committee (HREC) of the Peter MacCallum Cancer Centre (HREC reference number: HREC/74976/PMCC—2021; project number 21/93L). This project will be conducted according to the NHMRC National Statement on Ethical Conduct in Human Research (2007 and updates) [44] and the World Medical Association of Helsinki (2013 and updates) [45]. The trial is registered to the Australian New Zealand Clinical Trials Registry (ANZCTR) (ACTRN: ACTRN12622000792729).

### Informed consent

AYA will be assured that participation is entirely voluntary, and that they may stop their involvement in the evaluation project at any time. It will be explained that their decision will not impact on their care or relationship with the hospital.

### Data storage and privacy issues

A unique study identification number system will be used for data collected for this project linking AYA’s personal identifying information (e.g. names, URNs) with their corresponding study identification number (e.g. PT01/PT02) Data will be collected and managed in REDCap (Research Electronic Data Capture) hosted at the Peter Mac. Only members of the project team will have access to this data, in accordance with the National Statement on Ethical Conduct in Human Research 2007 and the Australian Code for Responsible Conduct of Research 2018.

### Withdrawal criteria

AYA who do not continue with the AYA Can-Sleep follow-up intervention will be asked if they consent to complete follow-up measures, evaluation, and for any of their existing data to be included in analyses. If consent is not given for the latter, their data will be erased from the database at the completion of the study, and any electronic or paper records pertaining to their involvement will be destroyed except medical notes that have been committed to the electronic system.

A record of AYA who have withdrawn from the study will be recorded and maintained on the secure REDCap database until the completion of the study. This is to ensure that these AYA are not approached again by the project team. AYA will be unable to withdraw their data after the completion of the study as their data may have already been used in analyses.

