## Abstract

**Background:**

Sleep problems are reported in up to 50% of adolescents and young adults (AYA) with cancer. Cognitive behavioural therapy for insomnia (CBTi) is considered the gold-standard treatment. In the AYA population, CBTi is associated with improvements in insomnia, daytime sleepiness, fatigue and quality of life. In adults, stepped-care interventions can improve accessibility to CBTi. This study aims to evaluate the acceptability and feasibility of a stepped-care CBTi programme in AYA with cancer.

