### Sample size

As this is a feasibility study, a power calculation to determine sample size was not undertaken. The target sample for screening is 80 AYA with cancer across a 15-week period. This is based on expected numbers of people seen in a large tertiary cancer centre and is in line with other sleep studies in the AYA population [6, 28]. This number is also consistent with recommendations for pilot and feasibility studies [29–31] and will provide data on the acceptability and feasibility of the AYA Can-Sleep programme.

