**Feasibility**				
Proportion of people approached who consent	-	X	X	X
> 50% indicates programme is feasible				
Dropout rate	-	X	X	X
> 40% indicates programme is feasible				
**Acceptability** — *quantitative and qualitative data*				
Participant experiences survey — screening questionnaires	5	X		
Participant experiences survey — post follow-up care	10		X	X
Clinician engagement survey	14			X
Other variables				
Demographic and cancer information	4	X		
Administrative and fidelity data		X	X	X

X, measure administered at that time point

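### The withdrawal rule allows dropouts to be left out of the dropout rate, and it loses other outcome data selectively from those who stop

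*Protocol article*

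**What the plan says.** All references are to the protocol article.

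- **Trigger (Withdrawal criteria).** "AYA who do not continue with the AYA Can-Sleep follow-up intervention will be asked if they consent to complete follow-up measures". The same question covers the evaluation and whether existing data may enter the analyses. The trigger is stopping the intervention, not withdrawing from the research.
- **Consequence (same section).** "If consent is not given for the latter, their data will be erased from the database at the completion of the study". In addition, "any electronic or paper records pertaining to their involvement will be destroyed except medical notes that have been committed to the electronic system".
- **Withdrawal log (same section).** For AYA withdrawn from the study, a log "will be recorded and maintained on the secure REDCap database until the completion of the study". The only purpose given is that the project team should not approach them again.
- **Feasibility criterion (Table 1, Feasibility rows).** The dropout rate is one of two measures with a threshold; the other is consent among those approached. The dropout threshold is printed as "> 40% indicates programme is feasible".
- **Other outcomes that need these data.** The Abstract and Operational data list retention, adherence, uptake and weeks of intervention completed as feasibility data. Data analysis judges impact by the number of AYA with a clinically meaningful improvement on the insomnia measures.

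**The concern.** Stopping the programme is the event that the dropout rate counts. It is also the event that sets off the second consent question and, without a yes, erasure. The people whose data can be removed are therefore those whose stopping has to be counted.

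Two things are at stake. First, the dropout rate: the article names no source for it that survives a refusal of data use, so an analyst could compute it from the remaining database and understate it. Second, the questionnaire and adherence data: those of refusers go whatever is done about the dropout rate. The loss falls only on AYA who stopped, so the counts of improvement and the acceptability results would rest on a set weighted towards those who continued. Because records are destroyed, neither problem could be repaired after study completion.

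**Working it through.** **1. Is there a plan figure to reproduce?** No. Sample size states that "a power calculation to determine sample size was not undertaken", and the 40% threshold is a set criterion, not a derived one. The check is a reading of the text followed by a sensitivity calculation.

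**2. Can dropouts be counted under the text?** Set side by side, the parts of Withdrawal criteria give:

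- Erasure takes place at study completion, and the log exists until then. Counting beforehand is possible.
- The consent sought is for inclusion in analyses. Late erasure does not by itself settle whether a refuser may be counted.
- The log covers those withdrawn from the study. The trigger covers those who do not continue the intervention. The two groups need not coincide.
- The log's stated purpose is to prevent re-approach, not to count dropouts.

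The text neither excludes refusers from the rate nor ensures that they are in it.

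**3. How large would the error be if erased AYA were excluded?**

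Inputs:

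- Screening target: "The target sample for screening is 80 AYA with cancer across a 15-week period".
- Prevalence: "Sleep problems are reported in up to 50% of adolescents and young adults (AYA) with cancer" (Abstract, Background).
- Starters *n*: 0.50 × 80 = 40. This is an assumption; it takes the upper prevalence figure and ignores referrals for sleep apnoea or restless legs. It is varied from 20 to 80.
- True dropouts *d* and erased dropouts *k*: not given in the article, so assumed and varied.
- Denominator of the rate: not given; taken as starters.

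Apparent rate = (*d* − *k*)/(*n* − *k*).

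This is at or below 0.40 when *k* ≥ (*d* − 0.4*n*)/0.6.

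| *n* | True rate | (*d* − 0.4*n*)/0.6 | Erasures needed | Apparent rate | Share of dropouts erased |
|---|---|---|---|---|---|
| 40 | 18/40 = 45% | 2/0.6 = 3.3 | 4 | 14/36 = 38.9% | 4/18 = 22% |
| 40 | 20/40 = 50% | 4/0.6 = 6.7 | 7 | 13/33 = 39.4% | 7/20 = 35% |
| 40 | 24/40 = 60% | 8/0.6 = 13.3 | 14 | 10/26 = 38.5% | 14/24 = 58% |
| 20 | 9/20 = 45% | 1/0.6 = 1.7 | 2 | 7/18 = 38.9% | 2/9 = 22% |
| 80 | 36/80 = 45% | 4/0.6 = 6.7 | 7 | 29/73 = 39.7% | 7/36 = 19% |

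If erased AYA left only the numerator, the understatement would be larger: 14/40 = 35.0% in the first row and 13/40 = 32.5% in the second.

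**4. And if dropouts are counted before erasure?** Then *k* = 0 for this purpose. The rates stay at 18/40 = 45%, 20/40 = 50% and 24/40 = 60%, and the bias is zero.

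**5. Which way does the decision move?** Excluding erased AYA always lowers the apparent rate. If 40% is a ceiling, that favours a finding of feasibility. As Table 1 is printed, a rate above 40% indicates feasibility, so a lower rate counts against it.

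**The case against.** The strongest reply is that the article never says refusers leave the dropout rate. A reader might infer that erasure does remove them. The documents do not support that: erasure comes only at study completion, a log runs until then, Operational data separately collects uptake, weeks completed and refusals, and Withdrawal criteria itself expects that data may have been analysed by the time the study is complete. This stands, and it limits the point about the rate to what the plan permits.

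Three further inferences also go too far.

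- **That the bias runs towards feasibility.** This treats 40% as a ceiling, which reverses the printed criterion. The printed direction looks implausible, but until it is resolved the direction of the effect on the decision is open.
- **That AYA who cannot be reached are erased.** The text says that AYA will be asked and what follows if consent is not given. It is silent on those who never answer.
- **That the rate will in fact cross 40%.** The number stopping and the share refusing data use are not in the article. With 20 of 40 stopping and 5 erased, the rate is 15/35 = 42.9%, still above 40%.

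It can also be said that letting participants decide on the use of their data is an ethics-approved choice, and that tabulation detail belongs in the full protocol. The first part is fair, and the fix below leaves that choice intact. The second does not dispose of the point, because the erasure rule is stated in the article and acts on the trial's own outcomes. The log does not clearly cure it, given its stated purpose and narrower scope.

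**Conclusion.** The point holds in a limited form. Withdrawal criteria ties stopping the intervention to a second consent and, without it, to erasure of data and destruction of involvement records. No statement secures the dropout count against this, so refusers may be left out of the rate. The loss of their ISI/ESS, survey and adherence data is not conditional on how the rate is computed, and it is selective among those who stopped.

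The possible understatement runs from zero (all dropouts counted before erasure) to enough to cross 40%. With true dropout at 45%, erasing about a fifth of dropouts suffices across 20 to 80 starters. At 50% with 40 starters it takes 7 of 20. These sizes rest on assumed numbers of starters, dropouts and refusals. The consequence for the feasibility decision cannot be stated until the printed direction of the dropout criterion in Table 1 is resolved.

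**What to change.** 1. In Withdrawal criteria, separate stopping the intervention from withdrawing data, so that the first does not by itself lead to the second.
2. For every consented AYA, keep a non-identifiable flow record: screen result category, step offered, step started, stage at stopping. Use it for all uptake and dropout figures whatever the decision on other data.
3. Report how many AYA had questionnaire data removed.
4. Subject to ethics approval, state that erasure follows an active refusal or request, and that non-response does not trigger it.
5. Resolve the printed direction of the 40% dropout criterion in Table 1 before the rate is used.

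The cost is a minor ethics amendment and a change to the consent form. No additional data are collected, and participants can still have their questionnaire data withdrawn. The change has to be in place before study completion, because destroyed records cannot be recovered.

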### Confidentiality

It is not expected that participating in this project will pose any risks of harm to participants. If any disclosures of risks to safety (e.g. suicidal ideation) occur during any stages of the project, standard clinical processes will be followed including safety planning with the participant and when needed advising an appropriate support person such as a member of the participant’s treating team and/or a family member. The limits to confidentiality are included in the PICF.

### Dissemination

Progress and outcomes of the project will be communicated and disseminated in a number of ways. Manuscripts will be prepared for publication in peer-reviewed journals. At the completion of the program, the treatment framework and project resources will be hosted on an online platform and disseminated to other interested organisations. Project findings will also be disseminated at national and international conferences. For the duration of the project, progress against milestones will be continuously monitored and reports provided to the Victorian Government Department of Health as per the funding requirements.

## Discussion

This study aims to evaluate the first known stepped-care programme to treat sleep difficulties in AYA with cancer. This study protocol is designed to assess valuable information regarding recruitment, prevalence and severity of sleep difficulties in the AYA population, retention and completion rates and the acceptability of a stepped-care programme to treat sleep difficulties to AYA and clinicians. These findings will help to assess the feasibility and acceptability of stepped-care CBTi as a standard approach to care in an Adolescent & Young Adult Cancer Service.

## Data Availability

Not applicable
